# I. Project Overview

The purpose of this project is to test the efficacy of an HIV prevention behavioral intervention to reduce sexual risk for HIV infection among non-injection, substance-using men who have sex with men (SUMSM). This study is a collaborative project with multi-site research teams funded through a cooperative agreement. The primary goal of the intervention is to reduce HIV transmission by reducing the incidence of unprotected anal sex while under the influence of alcohol and other drugs (AOD). In the focus group component testing phase of the project, we examined the feasibility and acceptability of **five** of six intervention sessions. In the pilot phase of the project, we followed one cohort (per site) through baseline assessment and the full six sessions of the intervention, including a follow-up session to gather feedback. **This protocol describes the trial phase only.**

## A. Protocol Summary

At an earlier date, we requested and received permission to conduct focus groups for component testing the individual two-hour sessions of a multi-session behavioral intervention, specifically testing sessions 1 through 5 of a six-session intervention. The overall purpose of the focus group component testing was (1) to assess feasibility and acceptability of content and flow of session activities, and (2) to gain insight into additional activities (besides those presented in the focus group) that may be useful in reducing sexual risk among substance-using MSM. After experiencing a particular intervention session, participants gave direct feedback about the session in a group discussion fielded by a staff person other than the facilitators who headed the intervention session. Each site conducted 2-9 focus groups that include a target of 8-10 persons per group (minimum 5, maximum 12). The present document includes revisions to the intervention sessions based on feedback and observations gained during the focus group phase.

The pilot phase enrolled one cohort at each study site, including intervention group and comparison group arms. A target of 5-10 men participated in each arm (intervention and comparison groups) of the cohort at each site, totaling 10-20 men per site and 40-80 men across sites.

## B. Study Sites

The focus groups, full pilot test of the intervention, and the intervention trial will be conducted - in conjunction with the CDC - in four sites: Chicago, Los Angeles, New York and San Francisco. Following are project staff and their respective institutions/sites:

# II. Introduction

## A. Background Information

Men who have sex with men (MSM) continue to be the largest risk category for incident and prevalent cases of HIV and AIDS in the U.S. (CDC, 2002). Studies of MSM have established an association between AOD use and risky sexual behaviors (Colfax et al., 2001; McKirnan et al., 2001; Purcell et al., 2001; Reback & Grella, 1999; Seage et al., 1998; Stall et al., 2001). AOD use exists in many MSM social contexts (e.g., bars, clubs, circuit parties) and may facilitate sexual risk (Halkitis et al., 2001; Mansergh et al., 2001; Purcell et al., 2001). In fact, Chesney and colleagues (1998) found recent drug use to be associated with recent HIV seroconversion. Although studies have assessed and confirmed the association of AOD use and unsafe sex, few have focused specifically on reducing sexual risk of SUMSM.

In a meta-analysis examining research on sexual risk reduction interventions for MSM (Johnson et al., 2002), nine controlled intervention trials were identified. Overall, they showed significant protective effects indicating that HIV interventions for MSM are generally effective at reducing sexual risk behaviors among MSM. However, none of these interventions specifically targeted non-injecting SUMSM. Thus, a gap exists in prevention efforts to reduce HIV transmission among SUMSM.

## B. Study Justification

The primary aim of the Project Mix overall is to develop and evaluate a practical intervention strategy that is specifically tailored to the needs of non-injecting SUMSM. The intent of the intervention is to decrease the number of unprotected anal sex partners (and acts) while under the influence of AOD and in general. This study is consistent with previously identified research priorities within NCHSTP.

The primary purpose of the **focus group phase was** to test the feasibility and acceptability by session of a pilot behavioral intervention to reduce sexual risk of MSM in the context of AOD use and in general. More specifically, the intent of the focus groups were :

- To observe and gain direct feedback from participants about whether and to what degree the intervention session activities work as intended;
- To assess the amount of time needed for the intervention session activities.

A secondary purpose of the focus group phase was to gather ideas about additional activities besides those presented in the focus groups that could be useful in reducing sexual risk among substance-using MSM.

Based on focus group findings, intervention session activities were revised for testing in the **pilot phase of the project**. The primary purpose of the pilot phase was:

- To observe and gain direct feedback from participants about whether and to what degree the intervention session and comparison group activities work as intended;
- To assess the amount of time needed for the intervention and comparison group session activities.
- To observe the flow of intervention and comparison group activities within and across the six sessions, including homework assignments;
- To observe the flow of procedures and materials, including HIV counseling and testing and ACASI survey assessment at baseline, randomization to groups at the time of Session 1, retention efforts, and data management.

This document presents the **full trial** protocol that includes revisions based on findings in the pilot phase of the study.

**III. Focus Group Phase of the Protocol** (IRB Approval Received September 2003)

**IV. Pilot Phase of the Protocol** (IRB approval received March 2004)

**V. Trial Phase of Project Mix**

**A. Methods**

## 1. Study Design

The purpose of the **study trial** is to test the efficacy of the six-session multi-component intervention arm versus the comparison arm. The intervention outcomes are to decrease frequency of unprotected anal sex in the context of alcohol/other drug (AOD) use and to decrease the number of unprotected anal sex partners. The intervention content is being revised after considering and incorporating information about feasibility and acceptability gained during the focus group phase (CDC IRB approval received on September 8, 2003) and the pilot phase (CDC IRB approval received March 2004). The trial includes screening, baseline assessment, HIV counseling and testing, six group sessions, and 3- 6- and 12-month follow-up assessments. Recruitment for the study trial will last approximately 21 months.

**2. Trial Cohort**

We plan to complete approximately 18-25 group cohorts per site. Each cohort includes one intervention group and one comparison group with 5-10 men (**mean of 7**) randomized into each group. Using active and passive recruitment methods, sites will recruit participants who meet the study eligibility criteria. “Active” recruitment includes outreach recruitment at street and venue locations where SUMSM socialize or congregate, such as bars, clubs, gay businesses, agencies and through websites and voluntarily-provided email address databases or listserves at each site. Sites will “passively” recruit men through flyers and information cards, and through referrals from local agencies and organizations, community advisory board members, and other study participants. Potential participants will be screened and, if eligible and willing to participate, will voluntarily provide written informed consent. A baseline visit will be conducted involving a behavioral assessment, HIV counseling and an HIV antibody test (except for HIV antibody positive men who provide documentation – see *Full Screening* section below). This baseline and testing session is expected to last approximately two and a half hours (range, 2-3 hours). At an assigned time, men in a cohort will return for Session 1 to be randomized to intervention and comparison group arms. Each of the six group intervention and comparison sessions will be held weekly unless extenuating circumstances arise. Each session lasts approximately 2 hours. Group sessions will be held in the following locations: New York Blood Center Project ACHIEVE research site at Union Square, New York City; a field office in Hollywood, California; Howard Brown Health Center and field offices in Chicago; San Francisco Department of Public Health AIDS Office, and a CBO in the East Bay, Oakland, California. For purposes of quality assurance (see section on Quality Assurance), the intervention and comparison group sessions will be audio recorded and observed occasionally by 1-2 staff members for review.

## 3. Study Population

### *a) Description of study population.*

The study population will consist of non-injecting HIV-negative and HIV-positive SUMSM who live in the four metropolitan areas under study (Chicago, Los Angeles, New York, and San Francisco). Being an important and unique characteristic of the sample, the balance of HIV status will be monitored throughout the study, and efforts will be taken to adjust and target recruitment efforts so that one serostatus does not exceed 60% of the sample. Each site will either recruit an ethnically diverse sample or conduct the group in a largely Latino or African-American geographic catchment area (to be determined and balanced across the four sites). For the study overall, sites will over-sample Latino and African American men for adequate representation due to high HIV prevalence rates among these populations. Similar to HIV status, race/ethnicity will be monitored throughout the study and recruitment will be adjusted and targeted with the intent of having relatively balanced proportions of Latino, Africa-American and white participants in the sample (approximately 30% for each group) and no more than 50% for any one race/ethnicity.

### *b) Participant inclusion criteria.*

To participate in the trial, the men must:

i. be 18 years of age or older;

ii. self-identify as male;

iii. understand and read English;

iv. live within the metropolitan area;

v. report being drunk or “buzzed” on alcohol 2 or more times or high on non-injection drugs at least once during (or two hours before) anal sex in the past six months;

vi. have had at least one unprotected anal sex episode in the past six months with a male partner of unknown or different HIV-status than their own (i.e., DUA)

### *c) Participant exclusion criteria.*

Men are ineligible to participate in the trial if they:

i. report only marijuana, only Viagra or only marijuana and Viagra use during anal sex (current research shows that marijuana use is not associated with sexual risk behavior);

ii. report injecting drugs (eligible if only methamphetamine, steroids, hormones and/or prescribed mediations) in the past six months;

iii. have known their HIV-positive status for less than six months (this is done to allow for psychological and behavioral adjustment following an initial HIV diagnosis and this time frame coincides with our screening window); these men (if they so desire) will be put on a wait list and contacted after 6 months have passed since their first HIV-positive test result;

iv. are currently involved in another HIV behavioral intervention study for MSM [local study site identifies a list of such studies in their community at the time of the trial];

v. have a specific plan to move from the metropolitan area within the next 15 months;

vi. participated in the pilot phase of the project;

vii. other reasons that the investigators deem would make participation either detrimental to the participant or to the study.

### *d) Estimated number of participants.*

The trial will be conducted to test the efficacy of a six-session behavioral intervention curricula. Given 30% attrition between baseline and randomization and 15% attrition between randomization and 12-month follow-up (see Table 3), a total of 1428-2000 men (357-500 per site) are needed at baseline in order to get at least 1000-1400 men at randomization (250-350 per site) and 852-1192 at 12-month follow-up (213-298 per site). Thus for a mean of 7 (minimum 5, maximum 10) men per group for each arm of a cohort, 18-25 group cohorts will be conducted at each site with a new cohort beginning approximately every 4-6 weeks (i.e., the week following completion of a cohort). Participants of the earlier pilot phase are not eligible to participate in the trial, however participants in the focus group phase are eligible for the trial.

**Table 3. Estimated number of participants in the trial to reach n=250-350 randomized in Session 1 and n=213-298 at 12-month follow-up per site.**

Baseline Randomization (Session 1)a Follow-up (12-month)b

n n *(18-25 cohorts x 7 [mean] per group x 2 arms)* n

----------------------------------------------------------------------------------------------------------------------------------------

Chicago 357-500 250-350 213-298

Los Angeles 357-500 250-350 213-298

New York City 357-500 250-350 213-298

San Francisco 357-500 250-350 213-298

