**4. Non-Randomized, No-Attention Control Arm (3rd Arm)**

Following completion of the final randomized cohort as outlined in section 2 above, 480 additional men (approximately 120 per site) will be enrolled in a non-randomized control arm of the study. These men will be recruited through similar strategies as the randomized men, required to meet the same eligibility criteria, and complete a full baseline assessment as described. They will, however, receive a different description of the study (i.e., two assessment appointments over 4.5 months) and a coinciding consent form (see Consent Form appendix). Third arm participants will receive a “3-month” follow-up assessment, however no subsequent follow-up appointments due to limited time and funds. At follow-up, we anticipate 85% retention (n=408, or approximately 102 per site), and with 80% power we could detect a change difference of approximately 15% or greater given the anticipated prevalence of our key outcomes for the control arm compared to either of the two randomized arms [see power analysis section]).

The 3rd arm men will not attend any group sessions or other appointments with study staff between the baseline and “3-month” assessment appointments. To account for similar follow-up time periods, the “3-month” follow-up for the Control Arm will actually occur 4.5 months after their baseline appointment (i.e., 3 months plus 6 weeks) to account for the 6 weeks of group sessions for each of the two randomized arms. Similar retention efforts will be employed for the Control Arm as for the other two arms both prior to the baseline appointment and prior to “3-month” follow-up. Participants will receive similar stipend amounts as the other two arms for their baseline and follow-up appointments.

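### Starting each cohort the week after the last one ends means a 6-week interval, not 4-6, and in about 21 months gives roughly 15-16 cohorts per site (840-896 men), below the stated 18 and 1000

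*Protocol*

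**What the plan says.** Four statements in section V.A of the protocol together fix the size of the randomized arms and the time available to reach it.

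- Study Design: "Recruitment for the study trial will last approximately 21 months".
- Trial Cohort: "We plan to complete approximately 18-25 group cohorts per site", and "Each of the six group intervention and comparison sessions will be held weekly unless extenuating circumstances arise". The section on the non-randomized third arm confirms the length of a cohort when it sets that arm's follow-up date "to account for the 6 weeks of group sessions for each of the two randomized arms".
- Estimated number of participants, on pace: "with a new cohort beginning approximately every 4-6 weeks (i.e., the week following completion of a cohort".
- The same section, on size: "Thus for a mean of 7 (minimum 5, maximum 10) men per group for each arm of a cohort", "in order to get at least 1000-1400 men at randomization (250-350 per site" are obtained. Table 3 builds the randomized number from cohorts, mean group size and two arms, then applies 15% attrition to reach 852-1192 at 12 months.

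**The concern.** The sentence on pace gives a numerical interval and then explains it with a rule that fits only its upper end. A site following the rule starts a cohort every 6 weeks. A site following the number may start one every 4 weeks, with two cohorts running at once.

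The choice matters because Table 3 makes the randomized number directly proportional to the number of cohorts. If the rule governs, the calendar does not deliver the lower end of the size that the protocol says it needs. The third arm begins only after the last randomized cohort is complete, and it already has a single follow-up because time and funds are limited. Delay would therefore fall either on the randomized number or on that arm. Overlapping cohorts also need more facilitators at once, since every group has two, so sites need to know which schedule applies.

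**Working it through.** **Inputs.** 18-25 cohorts per site and six weekly sessions (Trial Cohort); about 21 months of recruitment (Study Design); mean of 7 men per group, two arms, 15% attrition after randomization (Estimated number of participants and Table 3); four sites (Study Sites).

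**Step 1: reproduce the plan's size.** Men per site = cohorts x 7 x 2.
- 18 cohorts: 18 x 14 = 252 per site, x 4 = 1008 (stated: 250 and 1000).
- 25 cohorts: 25 x 14 = 350 per site, x 4 = 1400 (stated: 350 and 1400).
- 12 months: 0.85 x 250 = 212.5 and 0.85 x 350 = 297.5 (stated: 213 and 298 per site, hence 852 and 1192).

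Table 3 is internally sound. The question is whether the calendar yields that many cohorts.

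**Step 2: the interval implied by the rule.** With Session 1 in week 0, Session 6 falls in week 5. The following week is week 6, so back-to-back starts are 6 weeks apart. Any shorter interval means that a new cohort starts before the previous one has finished.

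**Step 3: the calendar.** 21 x 365.25 / 12 / 7 = 91.3 weeks. The lower cohort count is floor(91.3 / interval). The upper count adds one for a start in week 0. Assumptions: the first Session 1 is on day 1, Session 1 dates stay within the 21 months, there are no gaps, and each site runs one stream of cohorts.

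| Interval | 91.3 / interval | Cohorts per site | Randomized (x 14 x 4) | At 12 months (x 0.85) |
|---|---|---|---|---|
| 6 weeks | 15.2 | 15-16 | 840-896 | 714-762 |
| 5 weeks | 18.3 | 18-19 | 1008-1064 | 857-904 |
| 4 weeks | 22.8 | 22-23 | 1232-1288 | 1047-1095 |

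Against the minimum of 1000, the 6-week row is short by (1000 - 896)/1000 = 10% to (1000 - 840)/1000 = 16%.

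**Step 4: the reverse question.** The spacing needed lies between 91.3/n and 91.3/(n - 1).
- 18 cohorts: at most 5.1 to 5.4 weeks.
- 25 cohorts: at most 3.7 to 3.8 weeks, shorter than any stated interval.

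Time from first to last Session 1, at 4.348 weeks per month:
- 18 cohorts at 6 weeks: 17 x 6 = 102 weeks = 23.5 months.
- 25 cohorts at 4 weeks: 24 x 4 = 96 weeks = 22.1 months.
- 25 cohorts at 6 weeks: 24 x 6 = 144 weeks = 33.1 months.

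**Step 5: a more generous calendar.** A baseline assessment stays valid for 3 months, so some men could be randomized after recruitment closes. Add 13 weeks for this and subtract an assumed 4 weeks to fill the first cohort: 91.3 + 13 - 4 = 100.3 weeks. At 6-week spacing that gives floor(100.3/6) + 1 = 17 cohorts and 17 x 56 = 952 men. With no lead-in, 104.3 weeks gives floor(104.3/6) + 1 = 18 cohorts.

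**The case against.** The strongest reply is that the stated pace is 4-6 weeks and the parenthesis is loose wording. On that reading 18-23 cohorts fit and the minimum of 1000 is met. This stands. A reader might infer that the planned cohorts cannot be run in 21 months at any stated pace, and the documents do not support that. The shortfall against the minimum belongs to the back-to-back rule alone.

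Other replies carry part of their weight.

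- **The inputs are approximate.** The months, the cohort count and the interval are all given as approximate. That comfortably covers 25 cohorts at 4 weeks, which overrun by about one month. It covers 18 cohorts at 6 weeks less well, since they overrun by about 2.5 months.
- **Recruitment is not the same as Session 1 dates.** The 3-month validity of a baseline allows a tail. Even so, back-to-back running reaches 18 only if the first cohort starts with no lead-in, and the retention section expects each cohort to be recruited over several weeks.
- **Groups may be larger.** Sixteen cohorts reach 250 per site with a mean of 250/(16 x 2) = 7.8 men per group. This is within the 5-10 limits but above the planning mean of 7.
- **Sites may run parallel streams.** Chicago and San Francisco list more than one location. The protocol does not say that cohorts run there in parallel.

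Holiday gaps, and cohorts rescheduled because fewer than 12 men attend, work in the other direction. A reader might also infer that the trial is underpowered. No power loss can be shown from this document: it gives no power calculation for the randomized comparison, and the third arm is sized separately with its own power statement.

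**Conclusion.** The protocol contradicts itself on how often cohorts start, and the contradiction reaches the stated size of the randomized arms. Back-to-back running falls 10-16% short of the minimum randomized number under the assumptions in step 3, and about 5% short (952 against 1000) when late randomization and a 4-week lead-in are both allowed. With overlapping cohorts the lower and middle part of the range is feasible, and only the top end lies slightly beyond the period. The arithmetic is firm. What is uncertain is which schedule was intended. The point concerns the size of the randomized arms only.

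**What to change.** Reconcile Study Design, Trial Cohort, Estimated number of participants and Table 3 in one of two ways, without mixing figures from both.

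(a) **Overlapping cohorts.** Delete the parenthesis, state that cohorts overlap with starts no more than about 5 weeks apart, and restate the range as about 18-23 cohorts per site, 1008-1288 randomized and about 857-1095 at 12 months. The baseline column then becomes 1008/0.70 = 1440 to 1288/0.70 = 1840.

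(b) **Back-to-back cohorts.** Keep the parenthesis, drop the 4-5 week end of the interval, and then do one of the following:
- restate the size as about 15-16 cohorts per site, 840-896 randomized and about 714-762 at 12 months (baseline 840/0.70 = 1200 to 896/0.70 = 1280); or
- restate the recruitment period as about 23.5 months to the last Session 1 for 18 cohorts.

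The cost is a change of text and table, with no participants beyond those already planned. Option (a) lowers the upper end of the range and requires sites to staff overlapping groups. Option (b) accepts either a smaller trial, which would need its own justification because the present numbers are described as needed, or a later start for the third arm.

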**Total 1428-2000 1000-1400 852-1192**

----------------------------------------------------------------------------------------------------------------------------------------

a70% of baseline (30% attrition from baseline to randomization [Session 1])

b85% of randomization (15% attrition from randomization [Session 1] to 12-month follow-up)

